### Participant timeline {13}

Initially, volunteers will be numbered to avoid the risk of being identified. Soon after admission to the hospital, they will answer the standard anamnesis composed of questions about gynecological, obstetric, and health history, lasting approximately 10 min.

Before starting the intervention, the volunteer will be asked to mark the intensity of her pain at the moment on the VAS line. Immediately after and 30 min and 1 h after the interventions with the use of massage, TENS, or placebo, the request for pain intensity indication will be repeated.

After 12 to 24 h after the end of delivery, the volunteer will be visited by the researcher in the rooming-in and will be instructed to answer the intensity of pain in the VAS at this time, in addition to answering the QESP questionnaire. Then, birth and newborn data will be collected from the medical records.

The schematic diagram of the participant’s timeline can be seen in Fig. 3.

**Fig. 3 Fig3:**
[figure not shown]
Flow diagram of the trial design

### Sample size {14}

Based on a previous study by Báez-Suárez et al. [14], considering a difference between groups of 1.5 in VAS and a standard deviation of 1.61, considering an alpha of 0.05 and the power of the test of 0.80, the minimum sample size in each group is 36 participants.

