### Trial design {8}

This is a single-blind randomized controlled superiority trial to compare the three groups randomized in parallel (1:1:1). This article has been written in accordance with the Standard Protocol Items: Recommendations for Interventional Trials (SPIRIT) guidelines.

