### Outcomes {12}

#### Primary outcome measure

The primary outcome measure is change in the visual analog scale (VAS) from baseline to immediately after the intervention. The VAS is a simple one-dimensional instrument, used worldwide to assess pain intensity. It is characterized by a 10-cm-long horizontal line, where 0 represents no pain and 10 the worst imaginable or severe pain. They will be evaluated before the intervention and immediately after the intervention. All measurements will be performed in the period between uterine contractions.

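### The sample size of 36 per group does not follow from its stated inputs, which give about 19 to 20 for two groups and at most 26 under any usual three-group reading

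*Protocol article*

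**What the plan says.** The Sample size section {14} of the protocol article holds the only justification of the trial's size. Citing an earlier TENS study, it sets out its inputs as "considering a difference between groups of 1.5 in VAS and a standard deviation of 1.61", then concludes, "considering an alpha of 0.05 and the power of the test of 0.80, the minimum sample size in each group is 36 participants". The abstract repeats 36 for each of the three groups, which makes 108 women.

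Three other statements bear on the calculation:

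- Trial design {8} describes a superiority trial "to compare the three groups randomized in parallel (1:1:1").
- The primary endpoint is a change score: "The primary outcome measure is change in the visual analog scale (VAS) from baseline to immediately after the intervention".
- Statistical methods {20a} names analysis of variance for comparing the groups when the data are parametric.

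The sample size section does not mention sidedness, an adjustment for several comparisons, an allowance for losses, or whether 1.61 is the standard deviation of a single VAS score or of its change.

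**The concern.** The section gives every quantity the usual formula needs, so its result can be checked, and the result is nearly twice what the formula returns. Calling 36 a minimum makes it hard to read as a smaller requirement rounded up or padded for losses.

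What is at stake is how the result will be read. A reader will take the trial as having 80% power for 1.5 cm. On the stated inputs, power for 1.5 cm is far higher, and a difference of about 1.1 cm is detectable with 80% power. A null result would then be stronger evidence against a 1.5 cm effect than the text implies. A significant result could come from a difference well below 1.5 cm and still be taken as reaching the design target. The validity of the test itself is not affected.

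**Working it through.** **Inputs, all from Sample size {14}.** Difference δ = 1.5; SD σ = 1.61; α = 0.05, taken as two-sided because the section does not say; power 0.80; stated n = 36 per group. The standardised difference is d = 1.5/1.61 = 0.932.

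**Attempt to reproduce 36: two groups.** The normal formula is n = 2(z₀.₉₇₅ + z₀.₈₀)²/d² per group.

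- (1.960 + 0.842)² = 7.849 and d² = 0.868, so n = 2 × 7.849/0.868 = 18.08, rounded up to 19.
- The t test (noncentral t) gives 19.09, rounded up to 20.
- A one-sided α of 0.05 gives 15.

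**Attempt to reproduce 36: three groups.**

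| Reading at 80% power | n per group |
|---|---|
| Bonferroni, two comparisons (α = 0.025) | 22 (normal), 24 (t) |
| Bonferroni, three comparisons (α = 0.0167) | 24.1 → 25 (normal), 25.6 → 26 (t) |
| Tukey, pairwise | 25 |
| One-way ANOVA, one group differs by 1.5 (f = 0.439) | 17.7 → 18 |
| One-way ANOVA, means 0, 0.75 and 1.5 (f = 0.380) | 23.2 → 24 |

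The largest is 26, and 36 is not reached. Higher power does not explain it either: the two-group t test needs 26 at 90% and 31 at 95%.

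**Could losses explain it?** Going from 20 to 36 would need a loss of 1 − 20/36 = 44%. Going from 26 would need 1 − 26/36 = 28%. The section states no allowance, and the primary endpoint is taken immediately after a 30-minute intervention.

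**Where 36 might come from.** The document confirms neither of these.

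1. The total for two groups is 2 × 18.08 = 36.17. A total may have been recorded as a per-group figure.
2. The SD may have been larger than printed. An SD of 2.24 gives 36.0 per group by the t test. If 1.61 is the SD at a single time point and is converted to a change score with zero correlation between the two measurements, the SD is 1.61 × √2 = 2.28. That gives 36.2 by the normal formula and 37.2 by the t test.

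**What 36 per group provides if σ = 1.61 applies to the analysed change.**

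- Pairwise, two-sided 0.05: power for 1.5 cm is 97.4%. The difference detectable with 80% power is 0.670 SD, and 0.670 × 1.61 = 1.08 cm.
- Bonferroni for three pairs: power is 93.0%, and the detectable difference is 1.25 cm.
- Omnibus ANOVA: power is 94.7% with evenly spread means and 98.6% with one group differing.

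**What it provides under the second explanation.** With an SD of 2.28, pairwise power for 1.5 cm at 36 per group is 78.7%, close to the stated 80%.

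**The case against.** The strongest reply concerns the standard deviation. The primary endpoint is a change, and the section does not say whether 1.61 describes a change or a single score. If an undisclosed conversion to an SD of about 2.28 was made, 36 is essentially right, power is near 80% as stated, and the fault is only that a step was left out. This stands as a limit on the consequence: the figures of 97% and 1.08 cm hold only if 1.61 is the SD of the analysed variable. It does not rescue the sentence, because the printed inputs still fail to give the printed result.

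A second reply is that the comparison with 19 to 20 exaggerates the gap, because the trial has three groups and plans an ANOVA. This is partly right. Against 24 (evenly spread ANOVA) or 26 (Bonferroni) the excess is 36/24 − 1 = 50% or 36/26 − 1 = 38%, rather than the 80 to 89% found against 20 and 19. The fair range for the requirement is 18 to 26.

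A third is that too large a sample harms no inference. On the stated inputs the target power is indeed exceeded and no error rate is disturbed. The stated power and minimum would still be wrong.

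A fuller protocol or an analysis plan may record the missing step. It could show that an input printed here is incomplete, but it cannot make 1.5, 1.61, 0.05 and 0.80 yield 36.

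**Conclusion.** The point holds. The stated minimum of 36 per group is not the result of the stated inputs under any of the standard readings tried. Those inputs require 19 to 20 per group for a two-sided two-group comparison, and 18 to 26 across the ANOVA and multiplicity-adjusted readings. For three groups, 19 to 20 each means 57 to 60 women, against 108 planned.

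This rests on a two-sided α of 0.05, equal groups and a common SD of 1.61 for the change in VAS. On that basis the trial has about 97% pairwise power for 1.5 cm (93% with Bonferroni) and 80% power for 1.08 cm (1.25 cm with Bonferroni). If the SD of change is really about 2.24 to 2.28, power for 1.5 cm is about 79 to 80%, and the error lies in the SD as printed. Either way the justification is wrong as written and must be corrected, although nothing here calls for a different enrolment.

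**What to change.** Go back to the original calculation and rewrite the sentence in Sample size {14} so that a reader can reproduce it. State the comparison and test, the sidedness, the α per comparison, whether the SD is of a single score or of change, and any allowance for losses.

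- **If another SD or α was used,** print that value and show that it gives 36.
- **If 1.61 is the SD of change,** keep 36 and restate what it provides. For example: about 20 women per group are needed for 80% power to detect a 1.5 cm difference (SD of change 1.61, two-sided 0.05); 36 per group will be enrolled, giving about 97% power for TENS versus placebo, or 80% power for about 1.1 cm.

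The text should cite room for losses as a reason for the larger number only if that was the actual reason. The cost is one rewritten sentence, with no change to enrolment.

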### Recruitment {15}

Participants will be recruited at the Modesto de Carvalho Municipal Hospital, in the city Itumbiara, GO, Brazil. This hospital has an average of 67 births per month, with a rate of vaginal birth around 43.51%. No advertising is allowed for recruitment, and no inducements will be given to recruit patients into the study.

## Assignment of interventions: allocation

### Sequence generation {16a}

Participants will be randomized in a ratio of 1:1:1 to the three groups: group 1 (standard intervention and massage in lumbar region for 30 min), group 2 (standard intervention and TENS application in lumbar region), and group 3 (standard intervention and TENS placebo application in lumbar region for 30 min), using computer-generated random numbers.

### Concealment mechanism {16b}

A researcher not involved in the data collection will assign the groups using the sealed envelope method. The opaque envelopes will be numbered and kept locked, available only to the study researchers.

### Implementation {16c}

The allocation list will be generated by the mathematician who is part of the research team. All patients who give consent for participation and who meet the inclusion criteria will be randomized. After the participant has been included, the researcher responsible for the interventions will open the envelope with the lowest number available to determine which group the participant belongs to.

## Assignment of interventions: blinding

### Who will be blinded? {17a}

The researcher in charge of the interventions to be applied to the participants will be blind to the assessments. The researcher responsible for the evaluations and the researcher responsible for data processing will be blind for the treatment allocation. Parturients will not be totally blind to the procedure due to the difficulties imposed by the differences between techniques, but participants in the placebo group will not have information about the functioning of the equipment.

### Procedure for unblinding if needed {17b}

The loss of blinding should not be carried out unless there is a threat to the participant’s safety as a consequence of the study procedures.

## Data collection and management

### Plans for assessment and collection of outcomes {18a}

A trained researcher will perform all assessments during labor and after delivery. The VAS is a simple one-dimensional instrument, used worldwide to assess pain intensity. Studies demonstrate that the VAS is valid, reliable, and adequate to measure pain both in the clinical situation and in the evaluation of obstetric pain, in addition to being reliable to measure acute pain [22–24].

To assess the birth experience, the Childbirth Experience and Satisfaction Questionnaire (QESP) was chosen. It was built and validated in Portuguese and has good internal consistency and a test-retest fidelity index [21].

### Plans to promote participant retention and complete follow-up {18b}

Participants will be followed during their usual stay after delivery, which lasts 48 h in this hospital.

### Data management {19}

Following the institution’s protocols, all data will be considered anonymous, and participants will be identified by numbers. All source documents will be stored in locked file cabinets with secure and limited access. The data will be transferred to a secure online data cloud through double-checking between researchers. Only the research group has an individual password to access the data.

### Confidentiality {27}

The study will be conducted in accordance with the Brazilian rules and regulations. All data generated in this study will remain confidential. Only the research team has access to the study data. Access to data will only be provided in the event of audits or regulatory regulation by the institution.

### Plans for collection, laboratory evaluation, and storage of biological specimens for genetic or molecular analysis in this trial/future use {33}

Not applicable as no biological samples will be collected.

## Statistical methods

### Statistical methods for primary and secondary outcomes {20a}

Obstetric, gynecological, sociodemographic data, among others, will be compiled and collected using the statistical program Statistical Package for Social Sciences (SPSS Statistics version 23) and tabulated in the Excel program. The Shapiro-Wilk test will be applied to test the normality of the data, whether the data follow a normal distribution or follow a non-normal distribution.

The data will be presented to the normality of these, according to the quantitative variables that are normally distributed and continuously will be presented as mean (standard deviation). Continuous quantitative variables without normal distribution will be presented in median (interquartile range). Categorical variables will be assessed as frequencies and percentages.

For parametric data, a comparison between the groups will be carried out using the analysis of variance (ANOVA) test. Significance values lower than 0.05, at the 95% confidence interval, will be interpreted as statistically significant. The clinical relevance of the recorded values will be confirmed through effect size calculations (Cohen *d*) based on significant differences. The following effects will be taken into account: 0.00 to 0.49, low; 0.50 to 0.79, medium; and above 0.80, 312 high [25].

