### Objectives {7}

The aim of this randomized clinical trial is to verify the effects of non-pharmacological methods of pain relief added to the application of TENS on pain, satisfaction with childbirth, duration of labor, and the birth conditions of newborns.

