#### Secondary outcome measures

The secondary outcomes include change in the visual analog scale (VAS) from baseline to 30 min and 1 h after the intervention and in the immediate postpartum period (12–24 h after labor).

The participant’s satisfaction with childbirth will also be evaluated using the Experience and Satisfaction with Childbirth Questionnaire (QESP). This is a self-report questionnaire, with a total of 104 questions, which refer to the expectations, experience, satisfaction, and quality of the woman’s experience in relation to labor, delivery, and immediate postpartum. It consists of questions divided into eight subscales: (1) conditions and care provided, (2) positive experience, (3) negative experience, (4) relaxation, (5) social support, (6) partner’s support, (7) concerns, and (8) postpartum. The higher the score obtained in each of the subscales, the more positive is the perception of women in the dimension assessed by the subscale. The administration time for this questionnaire is approximately 30 min [21]. The questionnaire will be applied in the immediate postpartum period (12–24 h after delivery).

After delivery, information on the type of delivery, total duration of delivery, and possible obstetric complications will be collected from the participants’ medical records. Newborn data will also be collected from medical records: weight, height, possible complications, and Apgar score in the first and fifth minutes.

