### Methods for additional analyses (e.g., subgroup analyses) {20b}

None was planned.

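### Labor duration is compared without adjusting for parity, which gives up some precision on a secondary outcome at no saving

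*Protocol article*

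**What the plan says.** The aim in Objectives {7} covers "pain, satisfaction with childbirth, duration of labor, and the birth conditions of newborns". Under Secondary outcome measures, "information on the type of delivery, total duration of delivery, and possible obstetric complications will be collected" from the medical records.

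Neither the Eligibility criteria {10} nor the Exclusion criteria mention parity, so first-time and experienced mothers may both enter. Sequence generation {16a} gives a 1:1:1 allocation "using computer-generated random numbers" and names no stratum. Implementation {16c} adds none.

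Statistical methods for primary and secondary outcomes {20a} names one between-group test: "For parametric data, a comparison between the groups will be carried out using the analysis of variance (ANOVA) test". No covariate appears there. The section on additional analyses {20b} says "None was planned".

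Participant timeline {13} has every woman answer, soon after admission and before the intervention, a "standard anamnesis composed of questions about gynecological, obstetric, and health history". Parity is not named in the article, but an obstetric history would normally contain it.

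**The concern.** If first and later labors differ in length, parity is a source of variation in labor duration that is fixed before randomization. A one-way comparison of three groups counts that variation as error. The interval for a stated objective is then wider than it need be. If the groups happen to differ in their share of first-time mothers, nothing in the stated analysis takes this into account. The variable needed is very probably already on the admission form. Prespecification matters because a covariate chosen after the data are seen is open to challenge.

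**Working it through.** **Inputs from the protocol.** Three groups of 36, allocated 1:1:1. The protocol gives no mean, SD or target difference for labor duration, no parity mix and no parity effect, so it has no figure of its own to reproduce for this outcome.

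Its 36 per group was set for pain on the VAS (difference 1.5, SD 1.61, alpha 0.05, power 0.80). The usual two-sided formula gives 2 × (1.61 × (1.960 + 0.842) / 1.5)² = 18.1, or 19 per group, so 36 is not reproduced. At 36 per group the power for that VAS difference is about 97–98%. The mismatch is conservative and a separate matter. It matters here only because it shows that the primary comparison does not need this covariate.

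**Step 1. Share of variance due to parity (assumed).** Let g be the difference in mean duration between first and later births, in within-parity SDs, with half the women first-time mothers. Then R² = 0.25g² / (1 + 0.25g²).

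- g = 0.5: 0.0625 / 1.0625 = 6%
- g = 0.8: 0.16 / 1.16 = 14%
- g = 1.0: 0.25 / 1.25 = 20%
- g = 1.2: 0.36 / 1.36 = 26%

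A range of 5% to 30% covers these values.

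**Step 2. Gain from adjustment.** The equivalent unadjusted size is 36 / (1 − R²). The detectable pairwise difference at 80% power is √(1 − R²) × 2.802 × √(2/36), in units of the total SD of duration (normal approximation).

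| R² | Equivalent n per group | Detectable difference (SD) | Power for 0.5 SD |
|---|---|---|---|
| 0 (unadjusted) | 36 | 0.66 | 56% |
| 0.05 | 37.9 | 0.64 | 59% |
| 0.10 | 40.0 | 0.63 | 61% |
| 0.20 | 45.0 | 0.59 | 66% |
| 0.30 | 51.4 | 0.55 | 72% |

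Confidence intervals shorten by 1 − √(1 − R²), which is 3% at R² = 0.05 and 16% at R² = 0.30. With 108 women in three groups, the residual degrees of freedom fall from 105 to 104.

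**Step 3. Chance imbalance.** With a first-time share p, the SD of the difference in that share between two groups is √(2p(1 − p)/36), about 12 percentage points for p = 0.4 to 0.5. Simulating three independent groups of 36 gives a gap of at least 20 points in 7–8% of trials for one given pair, and in 17–18% for at least one of the three pairs.

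With 36 per group, the smallest such gap is 8/36 = 22 points. At that gap the shift in mean duration is 0.222g within-parity SDs. The unadjusted standard error is √(1 + 0.25g²) × √(2/36).

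- g = 0.5: shift 0.111, standard error 0.243, ratio 0.46
- g = 1.2: shift 0.267, standard error 0.275, ratio 0.97

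A gap of this size therefore moves the estimate by less than one standard error, and that standard error already allows for chance variation in parity.

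**The case against.** The strongest reply is that nothing here is wrong. An unadjusted comparison of randomized groups is valid, and a covariate list for a secondary outcome is the kind of detail an article may leave to a fuller protocol or analysis plan. The statement about additional analyses sits under a heading that gives subgroups as its example, so it does not clearly rule out adjustment of a main comparison. This stands to the extent that the point is not an error. But the article does name the comparison, and as named it has no covariate, so a better method can be proposed against the stated one. If a separate plan already includes parity, the article need only be aligned with it.

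Three further limits also stand:

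- The size rests wholly on assumed inputs. At the low end the gain is about two women per group.
- That parity is recorded is an inference from the obstetric history.
- The quoted ANOVA sentence covers parametric data only. If labor duration fails the Shapiro-Wilk check, that sentence does not govern it, so the fix has to address duration directly.

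A reader might infer that chance differences in parity will produce false effects on labor duration, or that the trial's main result is at risk. The documents support neither. Randomization keeps the comparison unbiased, the ordinary standard error allows for such differences, labor duration is secondary, and the sample was sized for pain. Nothing in the protocol argues for adding parity to the VAS comparisons either.

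**Conclusion.** The point holds as a free improvement limited to one secondary outcome. As written, the comparison of labor duration leaves parity in the error term. The cost is lost precision and no correction for an imbalance that happens to occur, without systematic bias. On the assumption that parity explains 5% to 30% of the variance, adjusting makes 36 per group worth about 38 to 51, and power for a 0.5 SD difference rises from 56% to between 59% and 72%. If parity explains little in this population, the gain is correspondingly small, and so is the cost.

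**What to change.** In Statistical methods for primary and secondary outcomes {20a}, add a sentence stating that labor duration will be compared with a linear model (ANCOVA) containing group and parity (first versus later birth), with parity taken from the admission obstetric history. State that duration is analyzed on a log scale if skewed, and that skewness is judged on the pooled data without group labels. Confirm that the admission form records previous births.

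The cost is one sentence and one degree of freedom. If parity is on the form, no new data are needed. Randomization need not change, so the sentence can be added while recruitment is under way, provided it is fixed before outcome data are compared by group.

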### Interventions

#### Explanation for the choice of comparators {6b}

In clinical practice, non-pharmacological methods of pain relief are used together, in an attempt to promote better results. However, no studies were found in the literature that verified, through the comparison of non-pharmacological methods of pain relief already recommended by the WHO and added to the application of TENS, whether such a resource would bring a potential reduction in pain in parturients during labor. Therefore, it was decided to compare non-pharmacological methods of pain relief with the same methods added to the use of TENS and placebo.

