#### Intervention description {11a}

The intervention of the three groups will take place during the first active phase of labor, from admission, which occurs when the parturient has 4 cm of cervical dilation, until the beginning of the expulsive period. The three groups will receive continuous support from professionals, encouraging walking and the adoption of vertical postures (standard intervention). In addition, parturients in group 1 will be positioned on a Swiss ball to receive a massage in the dorsal region for 30 min. Classic massage movements will be used, such as superficial sliding, deep sliding, kneading, friction, and rolling. Almond oil will be used to facilitate manual maneuvers.

Women in group 2 will undergo a standard intervention plus an intervention using TENS electrostimulation using the portable Neurodyn equipment (IBRAMED-Indústria Brasileira de Equipamentos Médicos EIRELI, Brazil). The parturients will be positioned seated on the Swiss ball, and four silicone electrodes will be fixed with masking tape in the thoraco-lumbar region, at the levels of T10–L1 and S2–S4. A frequency of 100 Hz and a pulse width of 100μs will be used, with intensity depending on the sensitivity of each patient for 30 min [17] (Figs. 1 and 2. Women in group 3 will undergo standard intervention and placebo intervention. They will be positioned and have electrodes attached in a similar way to group 2. However, the equipment will remain with the intensity button deactivated, without current flow (Figs. 1 and 2).

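### The only between-group test named is a three-group ANOVA, which cannot by itself show or refute an effect of TENS; the deciding contrast is left open

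*Protocol article*

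**What the plan says.** All references are to the protocol article.

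- **Question.** Objectives {7} sets out to "verify the effects of non-pharmacological methods of pain relief added to the application of TENS on pain" and other outcomes. Background and rationale {6a} gives the purpose as finding whether TENS adds anything to other non-drug methods, so as to inform equipment purchase. On comparators, section {6b} says "it was decided to compare non-pharmacological methods of pain relief with the same methods added to the use of TENS and placebo".
- **Arms.** All three groups receive the standard intervention. Beyond that, "parturients in group 1 will be positioned on a Swiss ball to receive a massage in the dorsal region for 30 min" (Intervention description {11a}). Group 2 receives active TENS. Group 3 has electrodes placed in the same way but no current.
- **Primary outcome.** "The primary outcome measure is change in the visual analog scale (VAS) from baseline to immediately after the intervention".
- **Analysis.** Section {20a} says "For parametric data, a comparison between the groups will be carried out using the analysis of variance (ANOVA) test" and then "Significance values lower than 0.05, at the 95% confidence interval, will be interpreted as statistically significant". It adds Cohen's d for significant differences. Section {20b} plans no additional analyses.
- **Sample size {14}.** One between-group difference of 1.5 on the VAS, SD 1.61, alpha 0.05 and power 0.80, giving 36 per group. Which groups the difference refers to is not said.

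**The concern.** A three-group ANOVA tests whether all three means are equal. The trial asks something narrower: whether TENS adds pain relief to the standard intervention. The two questions would be close if group 1 were a bare control, but it has an active component of its own. The background section itself cites studies in which massage reduced labor pain, so a difference driven by massage is a realistic outcome.

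A significant F test on the primary outcome would then be compatible with a TENS effect, a massage effect or both, and the article does not say which pair settles the matter. Cohen's d is a two-group measure, so pairwise statements are evidently intended. With no pair named beforehand, the pair to emphasize could be chosen after the results are known. At stake is whether the conclusion about TENS can be called confirmatory.

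**Working it through.** **Inputs.** Difference 1.5, SD 1.61, alpha 0.05, power 0.80 and n = 36 per arm, from Sample size {14}; three arms at 1:1:1, from Trial design {8}. Assumptions: two-sided testing, no dropout, normal data, and SD 1.61 applying to the VAS change in every arm. The article states none of these four.

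**1. The plan's own sample size.** For two means, two-sided, n = 2 × [SD × (1.960 + 0.842) / difference]² = 2 × [1.61 × 2.802 / 1.5]² = 18.1, so 19 per group (20 with the t distribution). A three-group ANOVA needs 18 per group if one arm differs by 1.5, or 24 if the means are 0, 0.75 and 1.5. The stated 36 is not reproduced by any of these, but it errs on the generous side. It is taken as given below.

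**2. Which contrast isolates TENS.**

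| Pair | What differs |
|---|---|
| Group 2 vs group 3 | Active against inactive TENS |
| Group 2 vs group 1 | TENS against massage |
| Group 1 vs group 3 | Massage against placebo TENS |

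Only the first pair holds everything else equal.

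**3. The F test when TENS equals placebo.** Let only the massage mean differ, by 1.5: means 1.5, 0, 0, grand mean 0.5.

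- Sum of squared deviations = 1.0² + 0.5² + 0.5² = 1.5.
- Noncentrality = 36 × 1.5 / 1.61² = 54 / 2.592 = 20.83.
- Effect size f = √(20.83 / 108) = 0.439.
- With 2 and 105 degrees of freedom the critical F is 3.08, and P(F > 3.08) = 0.986.

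So 98.6% of such trials give a significant ANOVA with no TENS-versus-placebo difference. The figure depends on the size of the massage effect. For a massage difference d the noncentrality is 36 × (2d²/3) / 1.61²:

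| d | Noncentrality | P(significant F) |
|---|---|---|
| 1.0 | 9.26 | 77% |
| 0.75 | 5.21 | 51% |
| 0.5 | 2.31 | 25% |

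**4. The named contrast.** The standard error of group 2 minus group 3 is 1.61 × √(2/36) = 0.379, and 1.5 / 0.379 = 3.95. Power at two-sided 0.05 is 97.4% (two-sample t) to 97.7% (normal approximation); with the pooled variance on 105 degrees of freedom it is 97.5%. With Bonferroni for all three pairs (alpha 0.0167) it is 93.0% (t) to 94.0% (normal).

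**5. Pairwise tests after the F test.** In simulated trials with 36 per arm, pairwise tests at 0.05 run only after a significant F test gave a family-wise error of about 5% when all means were equal (4.9% in 100,000 trials). They gave a false TENS-versus-placebo rate of about 5% when only massage differed by 1.5.

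**The case against.** **The 98.6% is not an error rate.** This stands. If massage truly differs, rejecting equality of three means is the right answer. The article nowhere calls a significant F test proof that TENS works, so a reader who infers that the plan would declare TENS effective whenever the ANOVA is significant goes beyond the text. What remains is that the one named test does not address the question asked.

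**Unadjusted pairwise follow-up need not inflate the error.** A reader might infer a family-wise error near 12%, the value for three pairwise tests run regardless of the ANOVA (12.2% by simulation). The article specifies no such route. Tests gated by a significant F test in exactly three groups stay near 5%, as shown above. A larger figure across the secondary outcomes would need the tests to be independent, which is implausible for repeated VAS scores and subscales of one questionnaire. It would also need tests of the categorical outcomes, for which only frequencies and percentages are planned.

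**Gating does not waste much power.** If TENS truly beats placebo by 1.5, gated power is about 97% when massage matches either arm and 94.5% when it lies halfway between. The plan asks for 80%.

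**Post-hoc detail may sit in an analysis plan that is not shown.** This stands for the mechanics of follow-up tests. It is weaker for the choice of deciding comparison, which should agree with the objective and the sample size, both of which are in the article.

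**The article does not make group 2 versus group 3 the sole interest.** True: Trial design {8} speaks of comparing three groups, and TENS against massage is a legitimate question. That supports giving the other pairs a defined place, not leaving the primary pair open.

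**Conclusion.** The point holds in a limited form. The article fixes a three-group ANOVA at 0.05 as its only between-group test, while its question is the added effect of TENS. Because group 1 receives massage, the ANOVA result alone can neither support nor reject a TENS effect, and the comparison that decides is not named. A massage-only difference of 1.5 makes the F test significant in 98.6% of trials; smaller massage effects make this less frequent (51% at 0.75). These figures rest on SD 1.61 for the VAS change in all arms, normal data, 36 evaluable women per arm and two-sided testing.

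The documents do not show an inflated type I error or a material loss of power. The defect is a mismatch between question and test, and it can be repaired without more participants.

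**What to change.** In section {20a}, state that the primary analysis is the contrast of group 2 minus group 3 on the VAS change from baseline to immediately after the intervention. Estimate it from the same three-group model, test it at two-sided 0.05 and report it with a 95% confidence interval. Then either test group 2 minus group 1 and group 1 minus group 3 in that order, each at 0.05 and only while the preceding test is significant, or name a gated or adjusted procedure for these pairs. Say that the secondary outcomes are supportive and will be reported with confidence intervals. In section {14}, say which pair the difference of 1.5 refers to.

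The cost is a few sentences and no added participants. The massage comparisons become secondary, and under the fixed sequence they lose confirmatory standing if the first test fails. If this counts as a major modification, section {25} requires a formal amendment, ethics committee approval and a change to the registry entry. It should be settled before anyone sees outcome data by group.
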